## Abstract

**Background:**

Dietary sulfur amino acid (SAA) restriction is an established animal model for increasing lifespan and improving metabolic health. Data from human studies are limited. In the study outlined in this protocol, we will evaluate if dietary SAA restriction can reduce body weight and improve resting energy expenditure (REE) and parameters related to metabolic health.

**Method/design:**

Men and women (calculated sample size = 60), aged 18–45 years, with body mass index of 27–35 kg/m^2^ will be included in a double-blind 8-week dietary intervention study. The participants will be randomized in a 1:1 manner to a diet with either low or high SAA. Both groups will receive an equal base diet consisting of low-SAA plant-based whole foods and an amino acid supplement free of SAA. Contrasting SAA contents will be achieved using capsules with or without methionine and cysteine (SAA_high_, total diet SAA ~ 50–60 mg/kg body weight/day; SAA_low_, total diet SAA ~ 15–25 mg/kg body weight/day). The primary outcome is body weight change. Data and material collection will also include body composition (dual X-ray absorptiometry), resting energy expenditure (whole-room indirect calorimetry) and samples of blood, urine, feces and adipose tissue at baseline, at 4 weeks and at study completion. Measures will be taken to promote and monitor diet adherence. Data will be analyzed using linear mixed model regression to account for the repeated measures design and within-subject correlation.

**Discussion:**

The strength of this study is the randomized double-blind design. A limitation is the restrictive nature of the diet which may lead to poor compliance. If this study reveals a beneficial effect of the SAA_low_ diet on body composition and metabolic health, it opens up for new strategies for prevention and treatment of overweight, obesity and its associated disorders.

*Trial registration* ClinicalTrials.gov: NCT04701346, Registration date: January 8th, 2021

**Supplementary Information:**

The online version contains supplementary material available at 10.1186/s12967-021-02824-3.

## Introduction

The past decade has seen the emergence of circulating amino acids as predictors of metabolic risk, and evidence implicates a role for sulfur-containing amino acids (SAA) in obesity-related metabolic disease [1, 2]. SAA include the essential amino acid methionine, which via the transmethylation and transsulfuration pathways can be converted to cysteine, a conditionally essential amino acid [3]. Cysteine is a precursor of glutathione, taurine and H_2_S, compounds with critical metabolic properties [4], including intracellular antioxidant defense, bile acid conjugation and cardiovascular function, vasodilation, immunomodulatory and signaling functions, respectively [5].

The main sources of dietary SAA are animal-derived foods, the intakes of which are typically high in Western societies [6]. A Western diet is associated with hypertension, heart disease, obesity, diabetes, and certain cancers. In animal models, dietary SAA restriction has been demonstrated to induce several beneficial metabolic effects [7]. The first study dates back to 1993, in which methionine restriction was demonstrated to increase the lifespan of rats [8]. Subsequent studies have showed that SAA restriction results in higher energy expenditure, enhanced insulin sensitivity and lower adiposity [9, 10]. In addition, SAA restriction triggers metabolic adaptations leading to increased mitochondrial biogenesis and transcriptional remodeling of lipid and glucose metabolism with reductions in circulating and tissue lipids, hepatic steatosis, oxidative damage and inflammation [11–15]. In human observational studies, particularly circulating total cysteine linearly correlates with fat mass, independent of other SAA [16]. Collectively, dietary SAA restriction in animals and human observational data suggest that higher methionine and cysteine availability promotes fat gain [14, 17].

The substantial body of experimental data on the role of SAA as potentially causal risk factors for obesity and its metabolic sequelae has not been translated into dietary recommendations in humans, mainly because of limited data from interventions in humans. One 16-week randomized controlled trial showed that fat oxidation was increased on a methionine restricted diet [18]. Recently, we showed that a 7-day study with a SAA restricted diet decreased plasma methionine, cystathionine, urinary total cysteine, and increased serum fibroblast growth factor 21 (FGF21) and lipogenic mRNAs in adipose tissue [19]. Because of the limited human data available, effects of dietary SAA restriction should be further addressed to translate beneficial findings from animal studies to human populations with overweight and obesity. In the trial branch of the *Sulfur amino acids, energy meTAbolism and obesitY* (STAY)-project we will perform a dietary intervention in participants with overweight and obesity to (1) evaluate if 8 weeks of dietary SAA restriction reduces overweight and obesity, and improves body composition and energy expenditure, and (2) identify potential mechanisms by which lowering dietary SAA may change metabolism in humans. In this paper, we outline the study protocol of the trial according to the SPIRIT initiative: Standard protocol items: Recommendations for interventional trials [20] (see Additional file 1 for checklist).

## Objectives

The overall objective of the trial is to establish effects of SAA restriction on body weight and related parameters of metabolic health including body composition (lean mass, total and compartmental fat mass [visceral fat mass, subcutaneous fat mass]) and resting energy expenditure (REE) in humans. Further, we aim to characterize the response to SAA restriction in plasma biomarkers and gene expression patterns related to amino acid, sulfur compounds, lipid and glucose metabolism as well as markers of appetite regulation, inflammation, adipokines and markers of liver status. The overarching aim is to translate findings from previous animal experiments to humans. For a complete overview of the outcomes and their methods of measurement, see “Assessment of primary and secondary outcomes” and Table 1.

**Table 1 Tab1:** Primary and secondary outcomes

Primary outcome	Measured by
• Body weight	• DXA

Secondary outcomes	Measured by
• Resting energy expenditure, respiratory quotient, substrate oxidation	• WRIC
• Changes in body composition including body fat compartments and lean mass	• DXA • Waist circumference • Hip circumference • Waist-hip-ratio
• Plasma and urine concentrations of SAA and related intermediates and compounds (sulfurome)	• LC–MS/MS
• Plasma lipoprotein profile, total fatty acid profile, and glucose, c-peptide and insulin changes	• LC–MS/MS, GC–MS/MS, ELISA, colorimetric and/or enzymatic methods
• Adipokines and satiety hormones	• ELISA
• mRNA expression of enzymes involved in SAA, lipid and energy metabolism in adipose tissue and white blood cells	• qPCR and untargeted analysis (mRNA sequencing)
• Vitamin status, including plasma folate and B12 and methylmalonic acid	• LC–MS/MS
• 24 h-urine urea nitrogen for nitrogen balance	• Modified Kjelldahl method • BUN-assay
• Changes in plasma biomarkers	• Untargeted analysis (metabolomics)
• Serum changes in FGF21	• ELISA
• Changes in markers of liver status: ALAT, ASAT, ɤ-GT, LD, ALP, CK and bilirubin	• Colorimetric and/or enzymatic methods
• Changes in gut microbiota	• Sequencing of fecal samples

*BUN* blood urea nitrogen, *DXA* dual-energy x-ray absorptiometry, *FGF21* fibroblast growth factor 2, *WRIC* whole-room indirect calorimetry, *qPCR* quantitative polymerase chain reaction, *ELISA* enzyme-linked immunosorbent assay, *MS, LC–MS/MS* liquid chromatography–mass spectrometry-tandem, *MS, GC–MS/MS* gas chromatography/mass spectrometry-tandem, *ALAT* alanine aminotransferase, *ASAT* aspartate aminotransferase, *ɤ-GT* gamma-glutamyltransferase, *LD* lactate dehydrogenase, *ALP* Alkaline phosphatase ALP, *CK* creatine kinase

## Methods and trial design

### Study setting and design

The study will be conducted at the Centre for Clinical Nutrition (CCN) at Institute of Basic Medical Sciences, University of Oslo (Oslo, Norway). This randomized controlled trial (RCT) will follow the Consolidated Standards of Reporting Trials (CONSORT) guidelines [21]. Both randomized groups will receive a full diet intervention with provision of meals and snacks for the duration of the study. The intervention starts after a 7-day run-in period, and lasts for 8 weeks. Participants will attend the CCN at baseline (week 0) and at week 4 and at the final visit (week 8) after start of intervention for clinical assessment, anthropometric measurements and for collection of biological samples. Follow-up conversations will be conducted by telephone and e-mail on a regular basis.

### Participants and eligibility

Recruitment is scheduled for March 2021 through March 2022 and men and women 18–45 years of age will be included. A timeline is illustrated in Table 2, and a flow chart outlining participant flow in Fig. 1. The upper age cut-off is set to avoid heterogeneity as blood concentrations of glutathione, which is closely associated with cysteine metabolism, decrease with increasing age, possibly due to higher requirements [22]. Healthy participants with overweight and obesity (BMI 27–35 kg/m^2^) will be recruited to participate in the trial. For screening purposes and in order to ensure that potential participants with BMI between 27 and 30 are not erroneously included due to high lean mass and low body fat percentage, they will be asked to additionally report their waist circumference (WC). Traditional WC cut-offs for the definition of overweight are > 80 and > 94 cm, for women and men respectively [23]. A follow-up phone call will be made to verify all the reported information. Screening will be performed 1–3 weeks prior to baseline. Exclusion criteria include smoking, suffering from any chronic disease, established co-morbidities, veganism (≥ 1 month), pregnancy or breastfeeding the last 3 months, significant weight loss (≥ 5%) over the last 3 months and high intensity training (interval running, crossfit, heavy strength training) more than 3 session per week. An overview of the inclusion and exclusion criteria is given in Table 3.

**Table 2 Tab2:**
[figure not shown]
Content for the schedule of enrolment, intervention and assessments according to SPIRIT requirements

*DXA* dual X-ray absorptiometry, *SAA*_*low*_ diet low in methionine and cysteine, *SAA*_*high*_ diet high in methionine and cysteine, *WRIC* whole-room indirect calorimetry

**Fig. 1 Fig1:**
[figure not shown]
Flowchart of the study. *SAA* sulfur amino acids

**Table 3 Tab3:** Inclusion and exclusion criteria

Inclusion	Exclusion
Age 18–45	Smoking
BMI 27–35 kg/m^2^	Chronic disease + co-morbidities
Healthy participants	Veganism (≥ 1 month)
	Pregnancy
	Breastfeeding the last 3 months
	Significant weight loss (≥ 5%) over the last 3 months
	High intensity training (interval running, Crossfit, heavy strength training) more than 3 sessions per week
Waist circumference > 80 cm for women and > 94 cm for men	

Recruitment of participants will primarily occur through social media campaigns accompanied by an informative web article about potential benefits of plant-based diets with low SAA content, and a screening questionnaire. If eligible, a follow-up phone call will be made to confirm and clarify information regarding inclusion and exclusion criteria. Eligible participants will sign an informed consent (Additional file 2, in Norwegian) where project design and measures for data collection, storage and future use are described. Data will be stored safely in an encrypted space provided by Services of Sensitive Data at the University of Oslo. A biobank for long-term storage of biological material will be created for future exploratory analyses. The study will be conducted according to the guidelines in the Declaration of Helsinki, and has been approved by the Regional Ethics Committee for Medical Research in South East Norway (Reference No: 123644) and the Norwegian Centre for Research Data (Reference No: 723047) in line with the current regulations on data protection.

### Procedures for run-in and prior to study visits

During the run-in week, participants will be asked to do the following: limit alcohol intake to comply with the Nordic Nutrition Recommendations (NNR, max. 5 g/days for women, max. 10 g/days for men); maintain their level of habitual physical activity with no more than 3 high-intensity sessions per week; and cease dietary supplementation. The participants will be encouraged to follow these general guidelines for the duration of the study. Twenty-four hours prior to the study visits, participants will be asked to avoid strenuous physical activity as well as caffeine and alcohol intake to comply with protocols for measurements of REE in the whole room indirect calorimeter (WRIC). In addition, they will be asked to avoid all food and liquid (except water) intake 12 h prior to study visits. Participants will be instructed to collect 24 h-urine, spot urine and a fecal sample prior to each visit.

### Randomization and methods against bias

Recruited participants will be randomized in a stratified block fashion to one of the two intervention arms to ensure similar numbers of participants in each group (Fig. 1). Block sizes will be random and a multiplicative of two (the number of intervention arms). Because body composition and SAA metabolism differ by sex [24], the randomization will be stratified to ensure equal number of males and females in each intervention arm. Randomization will be performed by a researcher unrelated to the study using the “blockrand” package in the R software (R Foundation for Statistical Computing, Vienna, Austria). The randomization code will be kept separate from the researchers and analysts until the end of study.

Blinding of the study participants and investigators is usually not possible in a dietary intervention. However, this trial will be double blind, since the base diet is identical for both groups and the only difference is whether they receive capsules with or without methionine and cysteine. Data analysts will be blinded to the group allocation during analysis of the primary outcome.

### Dietary interventions

#### Base diets and amino acid supplement

The base diet is identical in both intervention groups and consist of low-SAA plant-based whole foods and an amino acid powder without methionine and cysteine (XMET XCYS Maxamaid, Nutricia Norway AS, Oslo, Norway). The amino acid powder is used to achieve adequate protein intakes as the whole foods in the diet are relatively low in protein. The base diet including the powder provides approximately 15–25 mg/kg body weight of SAA per day. SAA content will be adjusted accordingly using capsules (see *Controlling the SAA content of the intervention* for details). The total energy content is 10460 kJ (2500 kcal) for men, and 9200 kJ (2200 kcal) for women. Nutrient and energy intakes are in line with the NNR [25], and calculated to not be hypocaloric. The total amount of energy/protein and SAA in the diets only differ by sex and not individual body weight. The protein intake will be ~ 0.8–1.2 g/kg body weight depending on the body weight of the participant.

A typical daily menu is given in Table 4. Methionine and cysteine are abundant in animal-derived protein and in certain fruits, grains, nuts and vegetables. Thus, the base diet is vegan-based without meat, fish, eggs, dairy products and certain plant-based foods. A list of low SAA-containing foods will be provided for the participants with the option for extra or ad libitium consumption of foods (Table 5). The foods from this list may also be used to supplement all recipes in the meal plan. Approximate daily energy content of the base diets including the powder will range from 45–60 E% from carbohydrates; 25–40 E% from fats and 10–20 E% from protein which is in line with the NNR. Regarding intake of alcohol, the participants will be advised to not exceed intake of 10 g/days for men and 5 g/days for women which is recommended by the NNR.

**Table 4 Tab4:** Example of a daily menu

Meal	Ingredients/foods
Breakfast	Oat meal and/or bread with fruits
Lunch	Salad with beans, different fruits and vegetables and vegetable oil and bread
Dinner	Vegetable casserole/vegetable soup/bean salad and bread
Supper	Vegetable soup or salad with bread
Snack	Nuts/fruits

2–4 amino acid powder free of methionine and cysteine is to be consumed as drinks throughout the day

**Table 5 Tab5:** List of extra foods

Foods		
Vegetables	Fruit	Spice/herbs/sweeteners
Iceberg lettuce	Pear	Dill, raw
Celery sticks	Plum	Chili red, raw
Tomato	Nectarine	Chilipowder
Onion	Strawberries	Pepper seasoning
Cabbage	Apricot	Curry powder
Mushroom	Watermelon	Basil, dried
Cucumber	Apple (2 apples/day)	Basil, raw
Eggplant		Oregano, dried
Asparagus		Apple cider vinegar
Sweet pepper, red		Lime/lime juice
Radish		Figs (as a sweetener)
Cauliflower (1 serving/day)		
Olives (10 pieces/day)		
Spinach		

Animal-derived foods are major sources of vitamin B12, and thus vitamin B12 depletion in persons following a vegan or vegetarian diet is always a concern [26]. To ensure sufficient intake of both macro and micronutrients, both groups will in addition receive a powdered drink mix without methionine and cysteine. The powder contains a balanced amount of essential and non-essential amino acids, carbohydrates, vitamins, minerals and trace elements. Flavor enhancers (Flavour Modjul® from Nutricia or an alternative enhancer selected from a pre-defined list) may be added to the drinks to mask the unpleasant taste of the mix.

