### Strategies to maintain compliance

The compliance to the dietary interventions or dietary advice is a considerable source of bias. In previous pilot data, the compliance was shown to be > 80% to dietary interventions, which is likely due to the provision of all intervention foods, and the relatively short intervention period of 7 days [19]. We will continue home delivery of foods in the base diet to increase the incentive to adhere to the plan. This delivery will also include a menu with recipes for each meal and information on daily intakes.

After screening and prior to baseline, each participant will be carefully educated through nutritional counselling with study dietitians or dietitian students in their final year of training. During the intervention, the participants will be offered regular consultations with the study dietitians per telephone for encouragement and continuous evaluation of participant adherence. During these phone calls, participants will receive counseling and advice to facilitate motivation and diet adherence. They will also be allowed to ask any questions relating to the intervention, meals and recipes, and raise any concerns. In general, study personnel will be available to the participants via e-mail regarding the intervention at all times.

To limit the effects on the participants’ social life during a restrictive diet, they will be allowed one ad libitum meal per week, but this meal should precede testing days by no less than three days. The content and amount of the ad libitum meals should be noted in the food diaries. For the final week of the intervention, the participants should adhere fully to the study protocol including the meal plan.

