### Statistical analysis

Our study design includes two intervention groups and three repeated measurements (baseline, 4 weeks, final visit). To control for correlated observations per subject per visit, the analysis of outcomes will be by linear mixed model regression. This model will include the treatment covariate, the visit covariate and their interaction term and a random term to control for within-subject correlation. The primary outcome variable is change in body weight. The interaction term will indicate change over time in body weight by intervention group. Depending on the pattern of missing observations and loss to follow-up, missing values will be handled with multiple imputations or model approaches (including linear mixed models which are robust to missing observations), and sensitivity analyses will be performed as recommended [40, 41].

We expect that there will be treatment heterogeneity indicating that effects may differ depending on covariate values at baseline. For example, baseline body weight is highly predictive and correlated to body weight change during an intervention. All models will thus be adjusted for the baseline values of the outcome variable. In addition, the models will be adjusted for the blocking factor used in randomization.

The analyses will be performed according to the intention-to-treat approach, but per-protocol (in which noncompliant participants are excluded) analyses will also be reported as recommended by the CONSORT guidelines [21].

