### Limitations

The trial has a number of limitations. The SAA content of both the SAA_low_ and SAA_high_ diets is slightly higher than in our pilot but methionine levels are in line with Plaisance et al. [18], where effects on substrate oxidation was reported. The reason for this elevation of SAA intake is a result of slightly increasing intakes of whole foods and lowering the intake of the unpalatable supplement. The recruitment of participants through social media campaigns may result in self-selection of health-conscious participants, but this is generally a concern in all advertisement towards participants. We also note that there is a trade-off between the level of control of food intake and external validity considering that most foods will be provided to the participants at a weekly basis. For example, in everyday life, regular grocery shopping and shared meals likely expose participants to higher availability of all foods as well as impulse purchases. However, we regard this level of control necessary in order to make robust conclusions about the effects of SAA restriction on metabolic health. Future studies should evaluate the feasibility of following a SAA restricted diet in everyday life. Another limitation is that we will not be able to assess any long-term effects of SAA restriction over the course of 8 weeks. However, results from our study can hopefully inform and aid in the design of future long-term dietary interventions with dietary SAA restriction. In terms of data collection, we are unable to assess relevant complications of overweight and obesity in which SAA restriction has proved effective in animal models. For example, dietary SAA restriction may be a potential therapeutic approach to treat hepatic steatosis and improve postprandial glucose tolerance, but we do not have the resources available to assess these outcomes in a rigorous manner and therefore rely on relevant biomarkers that may may aid in the elucidation of an SAA restricted diet on the progression of these diseases (see Table 1 for details). Finally, although the diets are isoenergetic, they are not tailored in macro- and micronutrient content according to need of each participant, but we emphasize that the aim of this trial is to compare two diets with large absolute differences in SAA and not relative to energy intake.

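### Baseline resting energy expenditure is measured but not used in the body-weight model: a possible, unquantified loss of efficiency, not a bias or a sample-size error

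*Protocol article*

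**What the plan says.** Four parts of the protocol article bear on this point.

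- **Supply.** Base diets and amino acid supplement: "The total energy content is 10460 kJ (2500 kcal) for men, and 9200 kJ (2200 kcal) for women", and "The total amount of energy/protein and SAA in the diets only differ by sex and not individual body weight". The Limitations section acknowledges that the diets are isoenergetic but that "they are not tailored in macro- and micronutrient content according to need of each participant".
- **Intake is looser than supply.** Participants receive a list of low-SAA foods "with the option for extra or ad libitium consumption of foods". Under Strategies to maintain compliance, "they will be allowed one ad libitum meal per week". Under Monitoring compliance and feasibility, they record meals not eaten and foods eaten outside the plan.
- **Measurement.** The abstract (Method/design) lists "resting energy expenditure (whole-room indirect calorimetry) and samples of blood, urine, feces and adipose tissue at baseline, at 4 weeks and at study completion". REE is a secondary outcome in Table 1, and its first value precedes the intervention.
- **Model.** The Statistical analysis section lists treatment, visit, their interaction and a random term for within-subject correlation. It then states "All models will thus be adjusted for the baseline values of the outcome variable" and adds the randomisation blocking factor. Sex is the only stratifier described under Randomization. REE is not among the covariates.

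**The concern.** The Statistical analysis section justifies its baseline adjustment by prediction: baseline weight is included because it is expected to predict weight change. The same reasoning may extend to REE. If everyone of one sex is supplied with the same energy, weight change in either arm should depend partly on the gap between that supply and the person's own expenditure. Baseline weight and sex capture some of the differences in expenditure. The calorimeter may capture more, and it does so before treatment starts.

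What is at stake is precision for the primary outcome. If the remaining REE variation predicts weight change, omitting it leaves the interval for the arm difference wider than it needs to be, although the data are already collected. Validity is not at stake.

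**Working it through.** **Inputs from the Sample size section.** Weight SD 6 kg; correlation 0.9 with decay 0.5 per visit; differences of 1 kg at week 4 and 3 kg at week 8; alpha 0.05; power 0.80; 46 evaluable; 60 randomised with 25% dropout.

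**1. Reproduce the 46.** Read the correlation as 0.9 between adjacent visits and 0.9^1.5 = 0.854 from baseline to week 8. The changes from baseline then have:

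- week-4 variance 2 × 36 × (1 − 0.9) = 7.20
- week-8 variance 2 × 36 × (1 − 0.8538) = 10.53
- covariance 36 × (1 − 0.9 − 0.8538 + 0.9) = 5.26

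The squared standardised distance for (1, 3) kg is (10.53 × 1² − 2 × 5.26 × 1 × 3 + 7.20 × 3²) / (7.20 × 10.53 − 5.26²) = 0.910.

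The 2-df Hotelling test has noncentrality N/4 × 0.910 with 2 and N − 3 df.

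- N = 46: noncentrality 10.46, power 80.5%. This is the smallest even N that reaches 80%, so the stated figure reproduces.
- N = 60 × 0.75 = 45: noncentrality 10.24, power 79.5%.

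Other readings do not give 46 with this test. For example, a baseline to week-8 correlation of 0.81 gives 58.

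**2. What the model leaves unexplained.** After adjustment for baseline weight, the week-8 SD is 6 × √(1 − 0.8538²) = 3.12 kg, a variance of 9.76 kg².

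**3. How much REE might explain (assumptions, not in the documents).** Suppose REE differs between people of the same sex and weight with SD 50 to 200 kcal/day, intake equals supply, and 7700 kcal corresponds to 1 kg. Over 56 days the SD in weight change is SD(REE) × 56 / 7700, and partial R² is its square divided by 9.76.

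| Assumed REE SD (kcal/day) | SD of weight change (kg) | Partial R² |
|---|---|---|
| 50 | 0.36 | 1.4% |
| 100 | 0.73 | 5.4% |
| 150 | 1.09 | 12.2% |
| 200 | 1.45 | 21.7% |

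If participants make up part of the gap by eating more or less, the SD shrinks in proportion and R² with its square. At 50% compensation, 12.2% becomes 12.2 × 0.25 = 3.1%.

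**4. Effect on the planned test at N = 45.** Multiply the covariance of the changes by (1 − R²), with the same R² at both visits, and take off one error df.

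| Partial R² | Power of 2-df test |
|---|---|
| REE not in model | 79.5% |
| 1% | 79.9% |
| 2% | 80.3% |
| 5% | 81.6% |
| 10% | 83.7% |
| 20% | 88.0% |

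**5. Break-even.** The table does not charge for chance imbalance in REE between arms. Going from one to two covariates with 45 participants multiplies the expected variance of the arm difference by about 41/40. REE must therefore explain at least 1 − 40/41 = 2.4% to pay for itself. If it explains nothing, the standard error is wider by √(41/40) − 1 = 1.2%. The first two REE rows of the table are thus no real gain.

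**The case against.** The strongest reply is that nothing here is wrong. Adjusting for the baseline outcome and the stratifier is conventional and unbiased, and the planned size does not rely on REE. That stands, which is why this is a point about efficiency only. It does not dispose of the point, because the article fixes a covariate set and gives predictive value as the reason for adjustment.

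Three stronger readings are tempting and are not supported:

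- **That known variation is being discarded.** No section states or quantifies that REE predicts weight change beyond weight and sex, and what REE shares with those two is already adjusted for. Supply is also not intake. Most listed extra foods are vegetables, fruit and seasonings, which limits upward compensation by that route. Uneaten meals, off-plan food and the weekly free meal are not limited in that way. The Limitations sentence speaks of macro- and micronutrient content and discloses a deliberate choice.
- **That adding REE is certain to narrow the interval.** It does so only above the break-even, and the documents cannot place the trial above or below it.
- **That the trial has no participants to spare, since 45 falls below 46.** The gap is one participant and one percentage point of power (79.5% against 80.5%). The mixed model also uses partial data from dropouts. A single week-8 contrast, SE 3.12 × √(4/45) = 0.93 kg, would have about 88% power for 3 kg. That is a different test from the one that produced 46, and the two figures should not be combined into one argument.

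**Conclusion.** The point holds as a modest, conditional improvement. The weight model omits a baseline variable that is already measured and that a sex-fixed energy supply makes a plausible predictor of weight change. There is no bias and no sample-size error.

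The possible benefit runs from nothing (partial R² below about 2.4%, standard error up to about 1% wider) to power of about 88% instead of 79.5% at partial R² 20%. The upper end requires intake close to supply and large REE differences at a given weight and sex, so it is optimistic. The whole range rests on assumed REE variation, 7700 kcal per kg and the chosen reading of the correlation decay. What favours making the change is the small, bounded cost rather than an established gain.

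**What to change.** In the Statistical analysis section, pre-specify baseline REE from the whole-room calorimeter as a covariate in the body-weight model, as follows:

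- **Visit-specific coefficient.** Enter it as baseline REE × visit, or place it in a model for the week-4 and week-8 changes. With baseline as one of three repeated measures, a main effect alone shifts levels and does not reduce the error of the group-by-visit contrast.
- **Baseline value only.** Week-4 and week-8 REE are post-randomisation outcomes and must not be used for adjustment.
- **Missing values.** Replace a missing baseline REE by its prediction from baseline weight and sex, so that nobody is dropped.

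Extending this to DXA fat and lean mass is optional, since no gain has been calculated for them. The diet is not affected. The cost is a sentence or two in the plan, one extra coefficient per visit, and about 1% in standard error if REE proves uninformative. No new data, visits or participants are needed. The change should be made before unblinding so that it cannot look data-driven.
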